### Sample size

The two primary endpoints are knee pain measured on the VAS and WOMAC physical function score. The minimum clinically important difference to be detected in OA trials is a change in pain of 18 mm (on 100 mm VAS) [44] and a change of six physical function WOMAC units (out of 68) [73]. Based on our previous data, we assume a common between-participant standard deviation of change of 30 mm for pain and 12 units for WOMAC physical function. These statistics indicate a smaller standardized effect size of interest (Cohen’s *d*) of 0.5 for the WOMAC measure than the *d* of 0.6 for pain. Since primary analyses will adjust for baseline of the outcome measure by ANCOVA, the sample size to detect the above effect sizes with 80% power taking into account a pre-post correlation of 0.50 is 48 patients per arm for WOMAC function and 33 per arm for VAS pain. We obtained the pre-post correlation from data from Lim et al., in which correlations of 0.58 and 0.77 were observed for pain and function respectively [74], and therefore our value of 0.50 is expected to be conservative. A further issue is that comparisons of the exercise alone arm with each of the PCST arms involve separate physiotherapists per arm and therefore clustering effects by physiotherapists need to be accounted for in the sample size and analysis. Prior data indicate that the intra-physiotherapist correlation for pain and function is likely to be at most 0.050 [74]. Assuming physiotherapists will each treat on average 7 patients (hence clustering design effect = 1 + 6*0.050 = 1.30), a total sample size of 63 patients per arm is required. Assuming 10% dropout increases the sample size to 70 per arm, or 10 physiotherapists treating 7 patients each. Slight loss of power is expected due to imbalances in number of patients per physiotherapist; however with access to 11 physiotherapists in the PCST arms this should be negated. The comparison of Exercise and PCST versus PCST alone arms will be performed ‘within-physiotherapist’ and hence does not suffer from these clustering effects. With 70 patients per arm the power is 93% to detect the WOMAC effect size and 98% for pain.

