### Statistical analysis

Comparisons will be performed using an intention-to-treat analysis using all randomized participants. This analysis will include all participants including those who have missing data and those who are not fully adherent to the protocol. Some attrition is anticipated despite the fact that we will implement procedures to minimize loss to follow-up and participant withdrawal, and maximize adherence. We will employ multiple imputation methods to handle missing data in the analyses. Standard diagnostic plots will check model assumptions. Effect sizes will be calculated with an effect size of 0.2 being small, 0.5 medium and 0.8 large. All tests will be two-tailed and carried out at the 5% significance level.

Demographic and clinical characteristics as well as baseline data will be presented to assess the baseline comparability of the intervention groups. These variables will also be examined for those participants who withdraw from the study. Descriptive statistics will be presented for each group as mean change (standard deviation, 95% confidence intervals) in the two primary outcomes from baseline to 12 weeks. Between-group mean differences and 95% confidence intervals will be estimated with a mixed effects linear regression model in which physiotherapists are treated as random effects and baseline scores of the primary outcome are entered as the covariate [75], together with adjustment for the stratification variables of site and gender. Secondary outcomes will be as above for normally distributed measures, or will use binary or proportional odds random effects regression models for binary or ordinal outcomes as appropriate. Standard diagnostic plots will check model assumptions. All tests will be two-tailed and carried out at the 5% significance level with no statistical adjustment for multiple testing.

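### The sample size paragraph scales its effects by an SD of change yet calls a pre-post correlation of 0.50 conservative; the two statements do not fit together, and power for WOMAC function depends on which is meant

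*Protocol article*

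**What the plan says.** All of this stands in the protocol article, section Sample size, unless noted.

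- The differences to detect are "a change in pain of 18 mm (on 100 mm VAS" scale) and "a change of six physical function WOMAC units (out of 68").
- On variability: "we assume a common between-participant standard deviation of change of 30 mm for pain and 12 units for WOMAC physical function". The standardised effects follow as 18/30 = 0.6 and 6/12 = 0.5.
- The calculation is for an ANCOVA adjusting for baseline, and its target is given as "the sample size to detect the above effect sizes with 80% power taking into account a pre-post correlation of 0.50". Before any allowance for clustering and dropout, the number so obtained "is 48 patients per arm for WOMAC function and 33 per arm for VAS pain".
- The choice of 0.50 is defended from an earlier dataset: "correlations of 0.58 and 0.77 were observed for pain and function respectively [74], and therefore our value of 0.50 is expected to be conservative".
- A design effect of 1.30 (intra-physiotherapist correlation 0.050, 7 patients per physiotherapist) brings 48 to 63 per arm for comparisons with exercise alone, and 10% dropout brings it to 70. The integrated versus PCST comparison is treated as unclustered, with 93% power for WOMAC function and 98% for pain at 70 per arm.
- The Statistical analysis section fixes the test: "All tests will be two-tailed and carried out at the 5% significance level".

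**The concern.** How the ANCOVA gain depends on the pre-post correlation r is decided by which SD is held fixed. With the SD of the score fixed, a higher r means less residual variance, so a value below the observed ones is cautious. With the SD of change fixed, a higher r means that the change score has already removed most of what baseline explains, so ANCOVA adds less; assuming a low r is then optimistic. The paragraph names the SD of change and draws the conclusion that belongs to the SD of the score.

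This matters most for WOMAC function, which sets the sample size and has the observed correlation (0.77) furthest from 0.50. The comparison with exercise alone is half of the primary hypothesis and was planned at 80% with almost nothing to spare. A null WOMAC result there would be read against a claimed margin of safety that may not exist. The Discussion also lists this sample size among the study's strengths.

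**Working it through.** **Inputs** (Sample size and Statistical analysis sections): two-sided 5% test; 80% power; differences of 6 units and 18 mm; SDs 12 and 30; r assumed 0.50; r observed 0.58 (pain) and 0.77 (function); design effect 1.30; 63 evaluable and 70 randomised per arm.

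**Formulas** (normal approximation), with f the ratio of ANCOVA residual variance to the squared SD used in d:

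- n per arm = 2 × (1.96 + 0.8416)² / d² × f
- power = Φ( (d/√f) × √(m/2) − 1.96 ), where m is the effective number per arm: 63/1.30 = 48.46 against exercise, 70 for integrated versus PCST.

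**The factor f.** Let s be the SD of the score, equal at both visits. The ANCOVA residual variance is s²(1 − r²), and Var(change) = 2s²(1 − r).

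- SD of the score in d: f = 1 − r², which falls as r rises.
- SD of change in d: f = s²(1 − r²) / [2s²(1 − r)] = (1 + r)/2, which rises with r.

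The two agree at r = 0.50, where both are 0.75. A simulation of the change version gave residual variances of 107.8 at r = 0.50 (formula 144 × 0.75 = 108.0) and 126.9 at r = 0.77 (formula 144 × 0.885 = 127.4).

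**The plan's own figures, f = 0.75.**

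- WOMAC: 62.79 × 0.75 = 47.09, so 48. Pain: 43.61 × 0.75 = 32.70, so 33.
- 48 × 1.30 = 62.4, so 63; 63/0.9 = 70.
- Unclustered power at 70 per arm: 92.7% (WOMAC) and 98.4% (pain).

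Everything stated reproduces, under either reading.

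**Away from r = 0.50.** WOMAC function against exercise alone, 63 evaluable per arm:

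| r | f, SD of change | power | f, SD of score | power |
|---|---|---|---|---|
| 0.50 | 0.750 | 81.1% | 0.750 | 81.1% |
| 0.58 | 0.790 | 79.1% | 0.664 | 85.6% |
| 0.77 | 0.885 | 74.4% | 0.407 | 97.1% |

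On the SD-of-change reading at r = 0.77:

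- n for 80% power is 62.79 × 0.885 = 55.57, so 56; × 1.30 = 72.8, so 73; /0.9 = 81.1, so 82 per arm, against the stated 48, 63 and 70.
- If all 70 per arm were evaluable, power against exercise would be 78.8%.
- Integrated versus PCST, 70 per arm unclustered: 92.7% falls to 88.2%.

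Pain against exercise goes from 92.7% at r = 0.50 to 91.4% at r = 0.58.

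**Sensitivity of the 74.4%.**

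- Unequal SDs: with k = baseline SD / 12-week SD, f = (1 − r²)/(k² + 1 − 2rk). At r = 0.77, power is 69% at k = 0.8, 71% at 0.9, 74% at 1.0, 79% at 1.1 and 84% at 1.2. It returns to the planned 81% at k of about 1.14. The floor is 69%, where f = 1 and the adjustment gains nothing over change scores.
- Clustering: at an intra-physiotherapist correlation of 0.025 the design effect is 1 + 6 × 0.025 = 1.15, m = 63/1.15 = 54.8, and power is about 79%.

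**The case against.** The strongest reply is that the label, not the reassurance, may be the slip. The article states no formula, and at r = 0.50 the figures cannot distinguish the two factors. If 12 and 30 are SDs of the score, 0.50 is cautious and WOMAC power at 0.77 is about 97%. The entry criteria lend this some weight. With equal SDs, an SD of change of 12 at r = 0.77 implies a score SD of 12/√0.46 = 17.7, while a uniform spread over the admissible baseline range of 25 to 68 has SD 43/√12 = 12.4. For pain, an SD of change of 30 at r = 0.58 implies a score SD of 30/√0.84 = 32.7, while scores confined to 40 to 100 cannot have an SD above 30. That bound applies if the qualifying score is also the baseline score, which the article does not say. This part of the objection stands. It rules out treating the SD-of-change reading as established, but it does not make the paragraph consistent.

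The second reply is that 74% is not firm. It rests on equal SDs, on a correlation carried over from another study, and on the value of 0.050 that the article itself calls a likely maximum for clustering. This also stands. A restricted baseline would, however, push k below 1, which lowers power on the literal reading.

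A reader might therefore infer that the reassurance is simply backwards and that the trial has 74% power. The document does not support that as a flat statement: it holds on one of two readings and under the assumptions above. Nor should the loss for integrated versus PCST be put at 93% to 85%. The 85% uses 63 per arm and so mixes in dropout; at 70 per arm the effect of the correlation is 93% to 88%.

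**Conclusion.** The paragraph is internally inconsistent: an effect scaled by the SD of change and the claim that a correlation below the observed ones is conservative cannot both stand when SDs at the two visits are roughly equal. The literal wording favours the SD of change, and the Primary outcome measures section also defines the outcomes as change at 12 weeks. On that reading, WOMAC function power against exercise alone is about 74% at r = 0.77, against 81% at the assumed 0.50: a loss of about 7 points, with a range of about 69% to 84% for SD ratios from 0.8 to 1.2. On the other reading it is about 97% and only the label is wrong. Pain is hardly affected either way. The stated sample sizes are arithmetically correct at r = 0.50, and the analysis model and randomisation are untouched. The severity is moderate.

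**What to change.** In the Sample size section, state whether 12 and 30 are SDs of change or of the score.

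- If of change: delete the claim that 0.50 is conservative, use the factor (1 + r)/2, state the equal-SD assumption, and restate WOMAC function power at 70 randomised per arm as about 74% (r = 0.77) to 81% (r = 0.50) against exercise alone. Restate the 93% for integrated versus PCST as about 88% at r = 0.77.
- If of the score: relabel the SDs; the reassurance can then stay.

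The cost is one reworded paragraph and, on the first branch, a less favourable stated power. Enrolment and analysis do not change.

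### The 93% and 98% power quoted for integrated versus PCST alone ignores the plan's own 10% dropout; with it the figures are about 90% and 97%

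*Protocol article*

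**What the plan says.** The Sample size section of the protocol article works in steps. It assumes a "common between-participant standard deviation of change of 30 mm for pain and 12 units for WOMAC physical function" and target differences of 18 mm and 6 units, so the standardised effects are 0.6 for pain and 0.5 for function. With ANCOVA on baseline, 80% power and a correlation of 0.50, it arrives at 48 per arm for function and 33 for pain. A design effect of 1.30 for clustering by physiotherapist brings the larger number to 63 per arm. The next step is "Assuming 10% dropout increases the sample size to 70 per arm".

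The paragraph then turns to integrated versus PCST alone. The same physiotherapists treat both arms, so it applies no clustering penalty. It closes with: "With 70 patients per arm the power is 93% to detect the WOMAC effect size and 98% for pain".

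The Statistical analysis section sets the test level: "All tests will be two-tailed and carried out at the 5% significance level with no statistical adjustment for multiple testing". It also says that some attrition is expected, and that all randomised participants will be analysed with multiple imputation for missing data.

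**The concern.** In this paragraph 70 is the number randomised and 63 is the number expected to supply outcomes. The closing sentence takes its power from 70, so it counts the 7 patients per arm that the plan has just assumed it will lose. The exercise comparisons, by contrast, are powered on 63.

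Both kinds of comparison belong to the primary hypothesis (H1), which sets the integrated programme against PCST alone and against exercise alone. A reader who compares the two power statements is comparing one figure after dropout with one before it, and nothing in the text says so. What is at stake is the accuracy of a stated power, not the adequacy of the design.

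**Working it through.** **Inputs** (Sample size section unless noted)
- Standardised effects: 6/12 = 0.5 (WOMAC function) and 18/30 = 0.6 (VAS pain)
- Pre-post correlation: 0.50, so the ANCOVA variance factor is 1 − 0.50² = 0.75
- Two-sided 5% level (Statistical analysis section), z = 1.96
- Design effect: 1.30 for the exercise comparisons, 1 for integrated versus PCST alone
- Dropout: 10%

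**Step 1: the plan's sample size.** n per arm = 2 × (1.96 + 0.8416)² × 0.75 / d².
- Function: 2 × 7.849 × 0.75 / 0.25 = 47.1, so 48
- Pain: 2 × 7.849 × 0.75 / 0.36 = 32.7, so 33
- Clustering: 48 × 1.30 = 62.4, so 63
- Dropout: 63 / 0.90 = 70

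Every stated number reproduces, and 70 is 63 inflated for dropout alone.

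**Step 2: the plan's power.** Power = Φ(d / √0.75 × √(n/2) − 1.96). At n = 70, √(70/2) = 5.916.
- Function: 0.5 / 0.8660 × 5.916 = 3.416; Φ(1.456) = 92.7%
- Pain: 0.6 / 0.8660 × 5.916 = 4.099; Φ(2.139) = 98.4%

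These round to the stated 93% and 98%, so the stated figures rest on all 70 per arm.

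**Step 3: the same formula after dropout.** At n = 63, √(63/2) = 5.612.
- Function: 0.5774 × 5.612 = 3.240; Φ(1.280) = 90.0%
- Pain: 0.6928 × 5.612 = 3.888; Φ(1.928) = 97.3%

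A noncentral t calculation gives 89.5% and 97.1%.

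| Analysed per arm | WOMAC function | VAS pain |
|---|---|---|
| Stated in the plan | 93% | 98% |
| 70 (no dropout) | 92.7% | 98.4% |
| 63 (10% dropout) | 90.0% | 97.3% |

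**Step 4: the exercise comparisons on the same 63.** The effective number is 63 / 1.30 = 48.5 per arm, which gives 81.1% for function and 92.7% for pain. The 80% target is met after dropout.

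**The case against.** **The sentence is conditional and true for 70 patients.** It is arithmetically right if 70 per arm are analysed, and the dropout figure stands in the same paragraph. But that paragraph defines 70 as the number randomised, so the condition is one that the plan does not expect to meet.

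**Multiple imputation keeps all 70 in the analysis.** It keeps the participants but does not by itself restore the information in unobserved 12-week outcomes. Auxiliary data could recover part of it, but the protocol claims no such gain. If imputation did restore it, there would have been no reason to go from 63 to 70.

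**A within-physiotherapist comparison removes between-physiotherapist variance.** This is the best technical point. Reducing the residual variance by the plan's upper intra-physiotherapist correlation of 0.05 gives 91.4% and 97.9% at 63 per arm, which nearly closes the gap. However, 0.05 is given as a maximum, and the stated figures do not include this credit: with it, 70 per arm would give 93.9% and 98.8%, not 93% and 98%. So 90% and 97% are the figures on the plan's own stated inputs, and a modest gain beyond them is possible.

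**The effect is small.** This stands. The sentence is a closing remark and sets no sample size, test or decision rule.

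**A stronger reading to resist.** A reader might combine the dropout with the correlation of 0.77 that the plan cites for function, hold the SD of change at 12, and infer that power falls to about 85%. The variance factor is then (1 + 0.77)/2 = 0.885, and 63 per arm gives 84.7%. But those inputs already give about 88% at 70 per arm, so most of the fall comes from the changed correlation and not from dropout. If 0.77 is instead put into the plan's own factor (1 − 0.77² = 0.407), power at 63 per arm is about 99%. The documents do not support 85% as a consequence of this point.

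**Conclusion.** The point holds as a reporting inconsistency. The power quoted for integrated versus PCST alone is before dropout, while the rest of the paragraph works after it. On the plan's own inputs it should read about 90% for WOMAC function and about 97% for VAS pain. For function the type II error is about 10.0% where the stated figure implies about 7%; for pain the change is close to rounding.

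This rests on 10% dropout in each arm, on no recovery of information from auxiliary data, and on no variance credit for the within-physiotherapist comparison. A reader might infer that the trial is underpowered or that the sample size is wrong. The documents do not support that: 70 per arm follows from the clustered exercise comparisons, which meet the 80% target after dropout, and integrated versus PCST alone stays well above it.

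**What to change.** Replace the closing power sentence of the Sample size section with wording such as: *Allowing for 10% dropout (63 of 70 patients per arm providing 12-week data), power is about 90% for WOMAC function and 97% for pain.* If the authors want to keep the larger figures, they should label them as power with complete follow-up and give the after-dropout figures beside them.

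The cost is one sentence and slightly less favourable numbers. Design, recruitment and analysis do not change.

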### Statistical analysis

Comparisons will be performed using an intention-to-treat analysis using all randomized participants. This analysis will include all participants including those who have missing data and those who are not fully adherent to the protocol. Some attrition is anticipated despite the fact that we will implement procedures to minimize loss to follow-up and participant withdrawal, and maximize adherence. We will employ multiple imputation methods to handle missing data in the analyses. Standard diagnostic plots will check model assumptions. Effect sizes will be calculated with an effect size of 0.2 being small, 0.5 medium and 0.8 large. All tests will be two-tailed and carried out at the 5% significance level.

Demographic and clinical characteristics as well as baseline data will be presented to assess the baseline comparability of the intervention groups. These variables will also be examined for those participants who withdraw from the study. Descriptive statistics will be presented for each group as mean change (standard deviation, 95% confidence intervals) in the two primary outcomes from baseline to 12 weeks. Between-group mean differences and 95% confidence intervals will be estimated with a mixed effects linear regression model in which physiotherapists are treated as random effects and baseline scores of the primary outcome are entered as the covariate [75], together with adjustment for the stratification variables of site and gender. Secondary outcomes will be as above for normally distributed measures, or will use binary or proportional odds random effects regression models for binary or ordinal outcomes as appropriate. Standard diagnostic plots will check model assumptions. All tests will be two-tailed and carried out at the 5% significance level with no statistical adjustment for multiple testing.

### Economic evaluation

The economic evaluation will assess the incremental cost of the integrated intervention compared with PCST and with exercise. In each case the incremental cost will be compared to the incremental benefits of treatment in terms of a clinically significant improvement in pain, a clinically significant improvement in function, and the difference in quality adjusted life years (QALYs). The incremental QALYs will be measured by the between group difference in the mean AQoL score over 12 months. A social perspective on costs will be taken and will include resource use incurred both by health services and by the participant irrespective of payment source. Health care costs will be calculated from the utilisation data and average unit costs for each item. We will not include the costs of training the physiotherapists in the delivery of PCST in the primary analysis. The inclusion of time/productivity gains is controversial and the cost effectiveness ratios will be calculated with and without these “indirect costs”. Confidence intervals for incremental cost effectiveness will be calculated directly using non parametric bootstrapping. In addition we will calculate a cost effectiveness acceptability curve based for a range of hypothetical money values of outcomes [76]. This will be done using individual cost and outcome data over the 12 months or, if adjustments for imbalance at baseline and clustering of patients by physiotherapist are necessary, analysed using a mixed linear regression model [77].

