### Secondary hypotheses

H2: An integrated intervention of exercise and PCST will be more efficacious in improving pain and self-reported physical function than either PCST or exercise alone at 32 weeks and 52 weeks.

H3: An integrated intervention will be more efficacious in improving psychological function, functional performance, quality of life, physical activity levels and perceived response to treatment than either PCST or exercise alone immediately following the intervention and at 32 weeks and 52 weeks.

H4: Exercise will lead to greater improvements in muscle strength than PCST; PCST will lead to greater improvements in psychological parameters than exercise; and an integrated intervention will lead to greater improvements in both strength and psychological parameters at measured time points.

H5: Adherence to exercise during the 9-month unsupervised follow-up period will be greater with an integrated intervention than with an intervention of exercise alone.

H6: An integrated intervention will be more cost-effective than an intervention of exercise or PCST alone when costs are compared and related to the effects of the intervention at 52 weeks.

H7: Specific patient baseline characteristics will moderate or predict treatment effects while pre- to post-treatment changes in the targeted cognitions, behaviours and physical impairments will mediate the effects of PCST and exercise on subsequent patient pain and disability.

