### Quality assurance and intervention integrity

Physiotherapist adherence to the PCST protocol and quality of delivery will be monitored and enhanced by regular (approximately fortnightly) team meetings with the site psychologist. Audio-recordings of each physiotherapy treatment session will be reviewed by the site psychologist with feedback provided to the physiotherapist. For the two treatment groups involving PCST, the site psychologists will formally rate approximately 10% of sessions using randomly selected treatment audiotapes. The Melbourne psychologist will rate those from Brisbane and vice versa following a period of training to ensure consistency of ratings. The physiotherapist delivery of the PCST treatments will be rated on two aspects: 1) adherence to the protocol using a yes/no format and calculated to give a percentage score; and 2) quality of the treatment using a 1–5 scale (1 being poor, 2 fair, 3 satisfactory, 4 very good and 5 excellent) for each of the following therapist behaviours: establishes/maintains rapport; remains on schedule with the protocol or makes appropriate adjustments when indicated; applies PCST protocol to participant’s situation and current challenges; encourages participant’s active involvement in the session; uses time effectively/appropriate pacing; demonstrates good interpersonal skills; demonstrates professionalism and clinical judgment; overall effectiveness/skill of the therapist.

In addition, an unblinded research assistant will randomly observe selected treatment sessions for all treatment arms at each physiotherapy clinic and provide feedback to the therapist. Group-specific quality assurance checklists will be completed by the research assistant during the session. The checklist contains items pertaining to the protocol such as therapist time spent solely with the participant, treatment notes completed, review of home practice and handouts provided, through to more complex items such as therapist observation of participant practicing the exercises, therapist use of the rating perceived exertion scale to review intensity of exercises and progression of weights if required and for those in the PCST treatment groups, new concepts introduced and explained. Lastly, participants will complete a questionnaire about their experience with the physiotherapist including whether they would recommend the physiotherapist to someone they knew.

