Adverse events and the use of co-intervention will be recorded in the logbook during the treatment period and via questionnaire at weeks 12, 32, and 52 in the follow-up phase. Adverse events will be defined as any problem from the exercises and/or pain coping skills that lasted for more than two days and caused them to seek treatment.

Information on health care costs and direct non-health care costs over the entire study period (52 weeks) will be collected by questionnaire. Direct health care costs will include costs of physiotherapy attendance, additional health provider visits (doctors, specialists, other health care professionals), investigative procedures, purchase of prescription and over the counter medication, home care and hospitalization. Direct non-health care resources will include number of lost days from work.

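### Against exercise, the integrated programme is not fully costed: PCST training is excluded and psychologist supervision is not captured, so its incremental cost is understated

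*Protocol article*

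**What the plan says.** H6 under Secondary hypotheses reads "An integrated intervention will be more cost-effective than an intervention of exercise or PCST alone when costs are compared" and relates those costs to effects at 52 weeks.

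The Economic evaluation section sets the viewpoint: "A social perspective on costs will be taken and will include resource use incurred both by health services and by the participant", whoever pays. The same paragraph states: "We will not include the costs of training the physiotherapists in the delivery of PCST in the primary analysis". It gives no reason and describes no analysis that adds training back. The only with-and-without variant it names concerns time and productivity costs.

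Other measures gives the data source, "Information on health care costs and direct non-health care costs over the entire study period (52 weeks) will be collected by questionnaire", and the items: "Direct health care costs will include costs of physiotherapy attendance, additional health provider visits (doctors, specialists, other health care professionals), investigative procedures", followed by medication, home care and hospitalisation. Table 4 gives the source as a questionnaire and the health system. Neither place has an item for psychologist time.

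Quality assurance and intervention integrity states: "Audio-recordings of each physiotherapy treatment session will be reviewed by the site psychologist with feedback provided to the physiotherapist". It adds team meetings about every two weeks and presents them as a means of improving delivery as well as monitoring it. The Discussion repeats that all sessions are reviewed and that regular meetings provide continuing supervision. The Psychologists section makes this an ongoing role, directed at the physiotherapists who deliver PCST.

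**The concern.** The effect side of the H6 ratio comes from physiotherapists who were trained in PCST, had their sessions reviewed by a psychologist and met that psychologist regularly. The cost side, as written, omits the training and has no visible route for the psychologist's time. Physiotherapists in the exercise-only arm receive neither input, so the gap does not cancel when integrated treatment is compared with exercise. It lowers the incremental cost and makes the ratio look better for the integrated arm.

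The Background gives lower cost to the health care system as one possible advantage of using a single therapist. A reader will therefore look to the economic result for evidence on this point, and the comparison with exercise would leave out part of what was used to obtain the effect.

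**Working it through.** The protocol states no unit cost and no cost-effectiveness ratio, so there is no monetary figure to reproduce. The only stated figure used is the arm size, as a base for volumes.

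**Arm size (Sample size section).** With n = 2(1.96 + 0.84)² × SD²(1 − r²) / difference², r = 0.50:
- WOMAC function, SD 12, difference 6: 2 × 7.849 × (144 × 0.75) / 36 = 47.1, so 48.
- VAS pain, SD 30, difference 18: 2 × 7.849 × (900 × 0.75) / 324 = 32.7, so 33.
- 48 × 1.30 = 62.4, so 63; 63 / 0.90 = 70 per arm. The stated figure reproduces.

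**Who receives the omitted inputs.**
- PCST training: the 11 physiotherapists (six Melbourne, five Brisbane) who deliver both PCST arms. Exercise-only physiotherapists are not trained in PCST (Physiotherapists section).
- Psychologist oversight: PCST physiotherapists only (Psychologists section).
- The 4-hour exercise workshop covers all 21 physiotherapists, and research-assistant observation covers all arms, so neither is the source of the imbalance.

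**Counted contact time.** There are 10 sessions per participant, of 25 min (exercise), 45 min (PCST) and 70 min (integrated, of which 45 min is PCST).
- Exercise: 10 × 25 = 250 min = 4.17 h.
- Integrated: 10 × 70 = 700 min = 11.67 h.
- Increment: 700 − 250 = 450 min = 7.5 h per participant. This takes attendance to be priced by session length.

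**Review not captured, per integrated participant.** The protocol does not say how much of each recording is heard, so the fraction is an assumption.

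| Fraction heard | PCST part only (450 min) | Whole session (700 min) | Share of the 7.5 h |
|---|---|---|---|
| 10% | 0.75 h | 1.17 h | 10% to 16% |
| 25% | 1.88 h | 2.92 h | 25% to 39% |
| 50% | 3.75 h | 5.83 h | 50% to 78% |
| 100% | 7.5 h | 11.67 h | 100% to 156% |

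The corresponding time per exercise participant is zero. The table assumes full attendance. If attendance falls equally in both arms, hours fall in proportion and the shares do not change. Fortnightly meetings would be extra, and their length is not given.

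**PCST workshop.** 11 physiotherapists × 4 days = 44 therapist-days. Spread over the 140 participants in the two PCST arms, this is 44 / 140 = 0.31 day each. At an assumed 6 to 8 h per day it is 264 / 140 = 1.9 h to 352 / 140 = 2.5 h, before tutorials, accreditation and psychologist time.

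**Integrated versus PCST alone.** The same 11 physiotherapists deliver both, so training cancels. Review of the PCST part is 450 min of recording in each arm and also cancels. A difference remains only if whole integrated sessions are heard: (700 − 450) / 60 = 4.17 h at full listening, 0.42 h at 10%.

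**The case against.** The training exclusion is stated openly and applies to the primary analysis only. That wording leaves room for a secondary analysis in a fuller plan that is not shown. Leaving one-off training out of a base case is a defensible convention, and spreading it over 140 trial participants treats a lasting skill as used up in the trial. This stands. Omitting training from the base case is therefore not in itself an error.

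The missing psychologist item is inferred from a list that need not be exhaustive, and the review sits under a quality assurance heading. Work done purely for trial fidelity can reasonably be left out of a routine-care cost, and part of the psychologists' role might fall under the declared training exclusion. This stands in part. The formal rating of about 10% of sessions is plainly a fidelity task. The review with feedback and the meetings are different: they recur throughout treatment and are meant to improve delivery. A participant questionnaire or health-service utilisation record would not be expected to show them, and no logging of those hours is described. If they do fall under training, they are excluded by the plan's own words.

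The volumes rest on assumed listening time and set psychologist hours against physiotherapist hours without prices. They also leave aside the other components of 52-week cost, such as medication, other visits and hospitalisation. This stands in full.

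**Conclusion.** The point holds for integrated versus exercise. Followed as written, the primary economic analysis excludes PCST training and has no listed item or source that would capture psychologist review and supervision, although it claims a social perspective. The integrated programme is then not fully costed, and its incremental cost against exercise is understated. The direction follows from which physiotherapists receive the inputs. The size in money cannot be derived. In time, the omitted review runs from about 0.75 h to 11.7 h per participant against a counted 7.5 h, and that range depends wholly on the listening assumption. The 44 therapist-days of workshop come on top.

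Three stronger readings are tempting and not supported:
- That H6 as a whole is biased. It has two comparisons, and against PCST alone the omitted inputs largely cancel.
- That the tested intervention is not costed, or that 156% of its incremental cost is missing. Physiotherapy attendance is costed. The 156% compares hours, not money, and needs every integrated session to be heard in full. Nothing shows that the H6 conclusion would change.
- That calling the programme physiotherapist-delivered is wrong. The protocol sets out the psychologists' role in several sections, and relabelling would be a matter of preference.

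This is a worthwhile improvement to one comparison within a secondary hypothesis.

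**What to change.** - Log psychologist hours for session review with feedback and for team meetings, by arm. Keep apart oversight done only for trial fidelity, such as the formal rating of about 10% of sessions.
- Pre-specify that cost-effectiveness of integrated versus exercise is reported with and without psychologist supervision and PCST training, in the way already planned for indirect costs. Price the hours at average unit costs and spread training over a stated number of patients.
- State the H6 conclusion against exercise in light of both results. If only the version without these inputs favours the integrated arm, say so.
- If the exclusion of training stays in the base case, give the reason and reconcile it with the social perspective.

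The cost is minor logging work and one further scenario. The downside is a less favourable cost figure for the integrated arm. No treatment, clinical outcome or sample size changes.
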